## 7.5 Reference Start Date and Study Day

Study Day will be calculated from the reference start date and will be used to show start/stop day of assessments and events. Reference start date is defined as the day of the first dose of study drug intervention ie, Day 0.

Study Day will be computed as follows:

- Study Day = (Date of event – Date of first dose of study drug)

In addition, day relative to vaccination will be derived for each vaccination dose. For example, day relative to the first dose will be equal to the Study Day. Day relative to the second dose will start with a value of 0 on the day of the second dose.

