### **10.1 Adverse Events**

#### **10.1.1 Reporting of Adverse events**

All local and systemic AEs that occur within 28 days after each vaccination observed by the Investigator or reported by the participant, will be recorded by the participants in the Diary of Symptoms and by the Investigators in the study CRF. For COV001, diary cards for the second vaccines will not be filled out for participants in groups 2f, 2g, 4c and 4d. For COV002, solicited and unsolicited AEs will be reported for 7 days only for group 1-3, 5, 7, 8, 11 and 12 and a subset of up to 3000 participants for groups 4, 6, 9, and 10. In COV003, solicited AEs will be reported for a subset of 200 participants.

SAEs and Adverse Events of Special Interest will be collected throughout the study period.

Adverse events will be coded using the Medical Dictionary for Regulatory Activities (MedDRA) Version 23 or higher.

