### 10.1.4 Unsolicited AEs

All AEs are unsolicited AEs unless categorized as solicited AEs. Unsolicited AEs from the start of each dose through 28 days (ie, day of vaccination and the following 27 days) will be summarized. Summaries will be produced of:

- Number of participants with unsolicited AEs by treatment group, system organ class and preferred term
- Number of participants with unsolicited AEs, assessed by investigator as possibly related to investigational product, by treatment, system organ class and preferred term
- Number of participants with unsolicited AEs  $\geq x\%$  in either treatment group, by treatment and preferred term where x may be 1, 3 or 5

In the summary of number of participants, should a subject experience multiple events within a SOC or PT, the subject will be counted only once for that SOC or PT.

A listing of all unsolicited AEs will be provided at the primary analysis.

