#### **10.1.5 Serious Adverse Events (SAEs)**

SAEs are those events recorded as “Serious” on the AE page of the eCRF. SAEs following the first vaccination to 364 days after the last vaccination will be summarized. Summaries will be produced of:

- Number of SAEs by treatment group, Medical Dictionary for Regulatory Activities (MedDRA) system organ class and preferred term
- Number of participants with SAEs by treatment group, system organ class and preferred term
- Number of participants with SAEs, assessed by investigator as possibly related to investigational product, by treatment group, system organ class and preferred term
- Number of participants with SAEs  $\geq x\%$  in either treatment group, by treatment and preferred term where x may be 1, 3 or 5

In the summary of number of participants, should a subject experience multiple events within a SOC or PT, the subject will be counted only once for that SOC or PT.

A listing of all SAEs including those prior to the first vaccination will be provided at the time of the primary analysis.

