AESIs following the first vaccination to 364 days after the last vaccination will be summarized. The number and percentage of participants with AESIs will be summarized by treatment group, and by treatment, AESI term, and PT. Should a participant experience multiple events within a PT, the participant will be counted only once for that PT according to the first onset date.

A listing of all AESIs will be provided at the primary analysis.

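### SAEs and AESIs are compared by arm only over the full follow-up period; supplementary tables for the 28 days after each dose would show an early excess more clearly

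*SAP*

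**What the plan says.** Section 10.1.6, in the text after Table 9, sets one period for AESIs: "AESIs following the first vaccination to 364 days after the last vaccination will be summarized". The statistic is a count and a percentage: "The number and percentage of participants with AESIs will be summarized by treatment group, and by treatment, AESI term, and PT". Section 10.1.5 uses the same period for SAEs: "SAEs following the first vaccination to 364 days after the last vaccination will be summarized". Neither section plans a table by time since dose.

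Four other places bear on the point.

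- Section 10.1.4 has a post-dose window: "Unsolicited AEs from the start of each dose through 28 days (ie, day of vaccination and the following 27 days) will be" summarised by system organ class and preferred term. It also defines the class broadly: "All AEs are unsolicited AEs unless categorized as solicited AEs". An SAE or AESI with onset in those 28 days is therefore counted there, as a preferred term.
- Section 7.5 supplies the timing variable: "day relative to vaccination will be derived for each vaccination dose". Day 0 is the day of the dose.
- Section 10.1.1 states that "SAEs and Adverse Events of Special Interest will be collected throughout the study period", so the onset data exist for both kinds of event.
- Section 4.1 triggers the interim and primary analyses by COVID-19 case counts and bases safety on the data available at that time.

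**The concern.** Some Table 9 events, such as anaphylaxis, convulsion, thrombotic events and Guillain-Barré syndrome, would be of most interest if they clustered soon after a dose. A table running from the first dose to the cut-off adds to such a cluster all the background events that occur later in both arms. The ratio between arms moves towards 1 and the noise grows.

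The 28-day unsolicited-AE tables help only in part. A Table 9 category such as thrombotic, thromboembolic and neurovascular events covers many preferred terms. A modest excess in the category could appear as isolated single-event rows across several system organ classes, with no category row to add them up. Those tables also do not separate serious from non-serious events.

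At stake is how readily a reader of the planned tables would notice an early imbalance in an AESI category or in SAEs.

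**Working it through.** The SAP gives no power, event count or background rate for SAEs or AESIs, so there is no planned figure to reproduce. The following is an illustration.

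**Inputs**

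- Participants: about 19,800 in the any-dose safety set (SAP Table A2). Allocation of 1:1, giving 9,900 per arm, is an assumption.
- Risk window: 28 days after each dose (Section 10.1.4). Two doses for everyone, with windows that do not overlap, is an assumption and gives 56 days.
- Background rate of an AESI category: assumed 0.5% per person-year, with 0.1% as a low case.
- Effect: assumed threefold risk inside the 56 days and none outside.
- Follow-up T from the first dose: 90, 120 and 180 days. The first volunteer enrolled on 23 April 2020 (Section 1.2). The last amendment entry is dated 17 November 2020, 208 days later. The other three studies began on 29 May or in June (Table 1).

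**Formulas**

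- Control events = 9,900 × rate × T/365
- Excess in the vaccine arm = 9,900 × rate × 56/365 × (3 − 1)
- Ratio over T days = (56 × 3 + T − 56)/T
- Power: exact conditional binomial comparison of two Poisson counts, two-sided 5%

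**Results at 0.5% per person-year**

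Excess = 9,900 × 0.005 × 56/365 × 2 = 15.2 events, whichever period is tabulated.

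| Period tabulated | Control | Vaccine | Ratio | Power |
|---|---|---|---|---|
| The two 28-day windows (56 days) | 7.6 | 22.8 | 3.00 | 0.75 |
| 90 days | 12.2 | 27.4 | 2.24 | 0.63 |
| 120 days | 16.3 | 31.5 | 1.93 | 0.55 |
| 180 days | 24.4 | 39.6 | 1.62 | 0.43 |

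The excess stays at 15.2 while its standard error, the square root of the summed counts, rises from √(7.6 + 22.8) = 5.5 in the windows to √(24.4 + 39.6) = 8.0 at 180 days. This is a loss of precision. The expected difference between the arms does not move.

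**Results at 0.1% per person-year**

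Excess = 9,900 × 0.001 × 56/365 × 2 = 3.0 events. Power is about 0.10 in the windows and 0.08 to 0.10 at 90 to 180 days. Neither table would detect an effect this rare.

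**The case against.** The strongest reply is that the plan already looks at the post-dose period. Section 10.1.4 counts every AE that is not solicited for 28 days from each dose, so SAEs and AESIs are in those tables. Single diagnoses such as anaphylaxis or Guillain-Barré syndrome can be read there as preferred terms. Section 10.2 grades the most extreme laboratory values, platelets included, in the 30 days after each dose in the studies that it pools. All SAEs and AESIs are listed at the primary analysis, and a DSMB reviews emerging safety data about every two weeks. This stands. A reader might infer from Sections 10.1.5 and 10.1.6 that these events have no post-dose window at all, and the document does not support that. What remains missing is the category row and the seriousness split by arm.

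A reader might also infer from the 364-day limit that a year of background events swamps the comparison. The only analyses planned in Section 4.1 are event-driven, with months of follow-up. At 420 days the same model gives a power of about 0.24, but that describes a later analysis which this SAP does not plan.

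Third, the safety output is descriptive, with counts and percentages and no planned 5% test. Power is used here only as a scale for how visible an excess would be. The model also favours the windowed table, because it sets the true risk period equal to the tabulated one. In addition, Table 1 allows one or two doses in COV001 and COV002, so real window counts would be smaller.

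Last, much of Table 9 is slow-onset or chronic immune-mediated disease, for which long follow-up is the right view. That is a good reason against making a 28-day table the lead AESI comparison, and none against adding one.

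**Conclusion.** The point holds as a gap in presentation. The SAP does not contradict itself here, and the planned full-period comparison is not biased: background events fall on both randomised arms and the expected risk difference is unchanged. What is lost is sensitivity to a category-level excess soon after dosing.

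At follow-up plausible for the planned analyses, the loss is about 12 points of power at 90 days (0.75 against 0.63), 20 at 120 days (0.75 against 0.55) and 32 at 180 days (0.75 against 0.43). These figures rest on the assumed 1:1 split, the 0.5% background, the threefold risk and two doses for all. At a background of 0.1% per year the choice of table makes almost no difference to power.

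The addition is worth making because the data are collected, the timing variable is already derived and the SAP already uses a 28-day window. The document gives no ground for replacing or demoting the full-period tables.

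**What to change.** Add one sentence to each of Sections 10.1.5 and 10.1.6. It should specify supplementary tables, by treatment group, of participants with SAEs and of participants with AESIs (by Table 9 category and preferred term) whose onset falls on Days 0-27 after dose 1, after dose 2 and after any dose. Use the day-relative-to-dose variable from Section 7.5 and the window of Section 10.1.4. Present these tables alongside the full-period tables, which stay as planned.

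The cost is repeated runs of existing tables. The downside is more output, with smaller counts in each table. Fixing the window in advance also avoids choosing one after a signal has been seen.

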### 10.1.7 Death

Listings of all death due to causes other than COVID-19 will be provided at the time of the primary analysis.

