At the time of the interim and primary analysis, the safety of AZD1222 as measured by defined safety endpoints or of potential risk in overall pooled data and in subgroups as appropriate will be evaluated. Note that whereas an individual study must accrue 5 cases to be included in the pooled efficacy analysis, all data from COV001, COV002, COV003 and COV005 available at the time of analysis will contribute to the safety analysis if meet the definitions for populations.

Analysis marked for primary manuscript only in this plan will be conducted by Oxford University.

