| All participants analysis set | All participants screened for the studies, to be used for reporting disposition and screening failures.                                                                                                                                                                                                                                                                                                                                                                                                                                                                                                |
| Any Dose for Safety           | All randomized adult participants who received at least 1 dose of study intervention (AZD1222 or control).
Participants who withdraw consent or assent to participate in the study will be included up to the date of their study termination.
Erroneously-treated participants (eg, those randomized to treatment A but are actually given treatment B) are accounted for in this analysis set by assigning them to the treatment they actually received. A participant who received at least one dose of AZD1222 is classified as AZD1222. This analysis set will be used for safety analysis. |
| Any Dose for Efficacy         | All participants in Any Dose for Safety but for groups in COV002, only efficacy groups (ie, groups 4, 6, 9,10) will be considered.
This analysis set will be used for efficacy analysis.                                                                                                                                                                                                                                                                                                                                                                                                            |
| Dose1 SD for Safety           | Only participants who received SD as the first dose of AZD1222 or in corresponding control group in Any Dose for Safety. The treatment assignment will follow the same rule of Any Dose for Safety analysis set. This analysis set will be used for safety analysis.                                                                                                                                                                                                                                                                                                                                   |

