### 10.3 Subgroup Analysis

Overview of AEs including factors below will be summarized by subgroup.

- Incidence of all AEs
- Incidence of solicited AEs
- AEs by severity
- Incidence of unsolicited AEs
- Incidence of SAEs
- Incidence of AESI
- Deaths other than due to COVID-19

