## **13. APPENDICES**

## Appendix A Overview of Analyses

**Table A1 Overview of Evaluation of Efficacy**

| Dose and regimen a | Population                       | N b      | Time period of endpoints | Case definition                                                             | Other case definition                                                                                           |
|-------------------------------|----------------------------------|---------------------|--------------------------|-----------------------------------------------------------------------------|-----------------------------------------------------------------------------------------------------------------|
| SDSD + LDS                    | 18 years and above, Seronegative | ~19000 c | From 15 days post dose 2 | Incidence of First SARS-CoV-2 virologically-confirmed d COVID-19 | Severe COVID-19
Hospitalised COVID-19
ICU COVID-19
Death COVID-19
Infection SARS-CoV-2 e |
| SDSD                          | 18 years and above, Seronegative | ~15600              | From 15 days post dose 2 | Incidence of First SARS-CoV-2 virologically-confirmed d COVID-19 | Severe COVID-19
Hospitalised COVID-19
ICU COVID-19
Death COVID-19
Infection SARS-CoV-2 e |
| First dose is SD              | 18 years and above, Seronegative | ~15800              | From 22 days post dose 1 | Incidence of First SARS-CoV-2 virologically-confirmed d COVID-19 | Severe COVID-19
Hospitalised COVID-19
ICU COVID-19
Death COVID-19
Infection SARS-CoV-2 e |
| Any dose e         | 18 years and above               | ~19200              | From dose 1              | Incidence of First SARS-CoV-2 virologically-confirmed d COVID-19 | Severe COVID-19
Hospitalised COVID-19
ICU COVID-19
Death COVID-19                                      |

a by treatment received

b Seronegative is not considered. The dose information is based on the spreadsheet from Oxford in Aug2020. Number is floored to 100.

c Sensitivity analysis of ITT by randomization to AZD1222 or control

d In a subset (COV002)

e Virologically-confirmed from RT-PCR or other nucleic acid amplification test.

f Required for safety evaluation

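### COVID-19 deaths and severe cases in about 600 randomised, dosed COV002 adults fall outside every planned death and severe-disease output

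*SAP*

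**What the plan says.** On the safety side, section 10.1.7 plans one output for deaths: "Listings of all death due to causes other than COVID-19 will be provided at the time of the primary analysis". The subgroup overview in 10.3 has one line for deaths, "Deaths other than due to COVID-19". Table A2, which fixes the safety sets and endpoints, lists reactogenicity, unsolicited AEs, SAEs and AESIs. It has no row for death or severe COVID-19.

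On the efficacy side, Table 6 defines hospital admission (WHO grade 4 or higher), severe disease (6 or higher), need for ICU (7 or higher) and COVID-19 death (grade 10). Section 9.1.2 turns these into secondary efficacy endpoints, and 9.2 ties their analysis to the Table A1 sets. The widest set there is Any Dose for Efficacy, used from dose 1. Table 3 describes it as "All participants in Any Dose for Safety but for groups in COV002, only efficacy groups (ie, groups 4, 6, 9,10) will be considered".

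Section 4.1 adds that "whereas an individual study must accrue 5 cases to be included in the pooled efficacy analysis, all data from COV001, COV002, COV003 and COV005" contribute to safety, provided the population definitions are met.

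**The concern.** Leaving COVID-19 deaths out of the safety listing avoids double counting only if the efficacy analysis covers the same people. Here it does not. A participant in a COV002 group outside 4, 6, 9 and 10 belongs to the safety set but to none of the efficacy sets. If that participant dies of COVID-19, the safety death outputs omit the death because of its cause, and the efficacy death endpoint omits it because of the group label. A ventilated survivor is missed for a different reason: severe disease is defined only as an efficacy endpoint, so there is no safety display to fall back on.

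What is at stake is a complete account of death and severe disease by arm in a pooled summary for marketing authorisation. Table 9 names vaccine-associated enhanced respiratory disease as an event of special interest, and severe and fatal COVID-19 by arm from dose 1 is a natural companion to that summary. In such sparse tables a few events can matter, although the SAP gives no event rate from which to say how many would be missed.

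**Working it through.** **Step 1. Trace each output to its set.** The last column asks whether a COVID-19 death or severe case in a COV002 group outside 4, 6, 9 and 10 would be shown.

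| Output | SAP section | Set | Shown? |
|---|---|---|---|
| Death listing | 10.1.7 | Safety (Table A2) | No; COVID-19 deaths excluded |
| Deaths in subgroup overview | 10.3 | Safety (Table A2) | No; same exclusion |
| COVID-19 death endpoints | 9.1.2.12 to 9.1.2.14 | Efficacy (Table A1) | No; not in the set |
| Severe, hospital and ICU endpoints | 9.1.2.1 to 9.1.2.3, 9.1.2.9 to 9.1.2.11, 9.1.2.15 to 9.1.2.17 | Efficacy (Table A1) | No; not in the set |
| SAE tables and listing | 10.1.5 | Safety (Table A2) | By preferred term, if recorded as serious; fatal outcome and WHO grade not specified |
| AESI summary and listing | 10.1.6 | Safety (Table A2) | By AESI term and preferred term, if classed as an AESI; same limit |

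**Step 2. Size the group.** The inputs are the any-dose N in Table A1 (about 19200, efficacy) and in Table A2 (about 19800, safety). Both come from the same August 2020 dosing spreadsheet, both ignore serostatus, and both are floored to 100.

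- Nominal: 19800 − 19200 = 600, and 600 / 19800 = 3.0%.
- Smallest, given flooring: 19800 − 19299 = 501.
- Largest, given flooring: 19899 − 19200 = 699.

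In Table 3 the two any-dose sets differ only by the COV002 group restriction, so by those definitions the whole difference is COV002 adults. HIV-positive and non-randomised groups are excluded from all sets by section 5. They are not part of this count.

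**Step 3. Test the second possible route out.** Section 4.1 requires 5 primary-endpoint cases before a study enters the pooled efficacy analysis, and states this for the interim and primary analyses. Two readings are open.

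- The rule reaches the secondary counts. Section 9.2.2.3 sends the remaining secondary endpoints to the primary method, and no exemption for from-dose-1 counts is written.
- The rule does not reach them. Table 3 puts no such condition in the definition of Any Dose for Efficacy. The separate 5-case threshold in 9.2.2.3 is per endpoint; it suppresses only the vaccine efficacy estimate and still shows the distribution by group.

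I put no figure on the first reading. Nothing in the SAP says which studies would fall short. The planned enrolments in Table 1 (1122 for COV001, 2070 for COV005) include groups excluded from all sets and are not on the same basis as the dosing spreadsheet.

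**The case against.** The strongest reply is that these events are not lost. The SAE tables by arm and the listing of all SAEs carry no exclusion by cause and run on the safety set, which has neither the COV002 restriction nor the 5-case rule. Enhanced respiratory disease is summarised as an AESI on that set to 364 days after the last dose. A DSMB also reviews emerging safety data about every 2 weeks (section 1.2). Any Dose for Efficacy already takes in seropositive, low-dose and single-dose participants, so the gap is narrow. No primary estimate or error rate is touched.

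Most of this stands. A reader might infer that a COVID-19 death in these groups would be invisible, or that the check for enhanced disease depends entirely on efficacy eligibility. The SAE and AESI plans support neither inference. What remains is that neither output is specified to show fatal outcome or WHO grade, and the SAP does not say whether COVID-19 endpoint events are recorded as SAEs. The reply therefore cannot assume that they are.

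A reader might also lean on the Table A1 footnote "Required for safety evaluation" to argue that the plan itself treats the any-dose row as a safety analysis. That footnote has no anchor in the table, and its neighbours' letters are visibly displaced. Attaching it to that row is a guess, and the point does not need it.

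**Conclusion.** The gap is real but limited. For about 600 randomised, dosed COV002 adults (501 to 699; about 3% of the safety set), a COVID-19 death or a WHO grade 6 or higher case is in no planned death or severe-disease output. It follows from stated exclusion rules, not from missing detail. The size assumes that the August 2020 counts in Tables A1 and A2 still describe the sets.

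It is tempting to go further and say that whole studies with fewer than 5 primary cases drop out of the death and severe-disease counts. The text allows that reading but does not settle it, so it should be raised as an ambiguity to close.

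I would rate this as a cheap improvement to make before analysis, not as a condition for going ahead.

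**What to change.** - In 10.1.7 and 10.3, list and tabulate all deaths by arm and by cause (COVID-19 or other) on the Any Dose for Safety set.
- Add counts by arm, from dose 1, of adjudicated hospitalised, severe, ICU and fatal COVID-19 on the same set, and state that the 5-case study rule in 4.1 does not apply to them.
- Leave vaccine efficacy estimation on the efficacy sets unchanged.

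The cost is SAP wording and a few extra tables. Sections 4 and 9.1 already send all virologically positive cases to the blinded adjudication committee, so no new data collection is needed. Case ascertainment may be less complete in the COV002 non-efficacy groups. A note under the new tables should say so.
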